**Figure 3: Trial design**

*Randomization*

*Recruitment*

*Compare*

19

clinics

2299

patients

(121

per clinic)

**Intervention**

Usual care

•

Integrated care

guideline

•

Outreach training

programme

**Control**

•

Usual care

19

clinics

2299

patients

(121

per clinic)

Follow

-

up:

Clinics

Patients

Follow

-

up:

Clinics

Patients

38 Eden and Overberg clinics

*(stratified by*

*health sub*

*-*

*district)*

INTERVENTION

*Training starts*

PATIENT

INTERVIEWS

Baseline (pre

-

intervention)

Follow

-

up

12

-

16

months post recruitment

Initial:

8

-

12 sessions

over 4 months

Maintenance:

Quarterly

Ongoing

###

### Data analysis

Outcomes will be analysed on an intention-to-treat basis. For the primary outcome, a logistic regression model will be used to evaluate the effect of the intervention with stratification as a co-factor. The model parameters will be estimated by the generalised estimating equations (GEE) approach which takes into account the clustering of patients within clinics. Odds ratios will be presented with 95% confidence intervals.

Secondary analyses include: (a) analysis of the primary outcome but restricted to the subgroup of patients in whom control at baseline has been determined to be inadequate (e.g. treatment intensification among hypertensives with BP >140/90 at enrolment, treatment intensification among diabetics with HbA1C >7% at enrolment, treatment intensification among patients with chronic respiratory disease and frequent and/or severe symptoms as measured by the St George’s Respiratory Questionnaire (symptoms and activity components), treatment intensification among patients not receiving treatment for depression at enrolment); (b) extent to which the intervention effect is modified by co-morbidities by comparing intervention effectiveness across co-morbidity subgroups (1, 2, 3 or 4 or more chronic diagnoses) and the use of joint modeling techniques; (c) extent to which the intervention effect is modified by control and adherence, measured using the Revised 10-item Hill-Bone Blood Pressure Compliance Scale for South Africa. This last analysis will be restricted to patients with hypertension.

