### Study design

The study is a pragmatic cluster randomised controlled trial with clinics randomised to two parallel arms, and outcomes assessed on individual patients. Clinics will be randomised within health sub-district strata. Stratification is necessary to control for differences in the ratio of infectious to chronic diseases within communities within the Western Cape. Randomisation will be carried out by the trial statistician before the intervention is implemented or patients recruited.

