**Table 1: Primary outcomes and revised sample sizes**

| **Target condition** | **Primary outcome** | **Control** | **Int** | **ICC^1^** | **Required cluster size** | **Cumulative required per clinic** |
| --- | --- | --- | --- | --- | --- | --- |
| Diabetes | Treatment intensification:  Increase in dose of oral hypoglycaemic/ insulin *or*  Addition of new oral hypoglycaemic / insulin *or*  Addition/ increase in dose of ACE inhibitor *or*  Addition of aspirin *or*  Addition/ increase in dose of statin | 0.25 | 0.36 | 0.04 | 60 | 60 |
| Hypertension | Treatment intensification:  Increase in dose of antihypertensive medication *or*  Addition of new antihypertensive *or*  Addition of aspirin *or*  Addition/ increase in dose of statin | 0.25 | 0.36 | 0.04 | 60 | 90^2^ |
| Chronic respiratory disease | Treatment intensification:  Addition of beta-agonist *or*  Addition of ipratropium bromide *or*  Addition of oral theophylline *or*  Addition/ increase in dose of inhaled corticosteroid | 0.15 | 0.25 | 0.02 | 27 | 90^3^ |
| Depression | Case detection:  Started on antidepressant medication *or*  Referred for counselling *or*  Referred to psychiatric services | 0.04 | 0.10 | 0.04 | 60 | 105^4^ |

^1^ ICC: intracluster correlation coefficient

^2^ Assumes 50% of those with diabetes also have hypertension (Steyn 2008 i)

^3^ Assumes 33% of those with either diabetes or hypertension will have a chronic respiratory disease (Ho 2008)

^4^ Assumes 50% of those with diabetes and/or hypertension and/or chronic respiratory disease will score 10 or more on the CESD-10 (Prince 2007).

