## Research procedures and data collection

Participants who are eligible and provide consent for the validation study will be asked a few questions to establish smoking status, treatment for hypertension and diagnosis of diabetes, and will undergo the following measurements: blood pressure, height, weight, hip and waist circumference. Blood pressure will be taken using an electronic device, and will follow the American Heart Association protocol, where multiple measurements (three) are taken over the period of the interview a minimum of two minutes apart. The average of these readings will be used (Pickering 2005). Participants in the validation study will also undergo venesection and blood will be drawn for triglycerides and HDLC/LDLC ratio. Trial participants with diabetes requiring medication will undergo an HbA1C. Venesection will be performed by the usual nurses responsible for phlebotomy at the clinic, but bloods will be transported to and analysed by a private pathology service. The need for these exploratory assessments and analyses is illustrated by the finding that in community surveys in the target areas, the HDLC to TC ratio was found to be higher than in Caucasian populations (Mollentze 1995, Steyn 1989, Oelofse 1996). This suggests that TC levels will not serve as a satisfactory proxy measure for cardiovascular risk associated with apo B-related lipoprotein particles such as LDLC. We therefore propose to explore whether HDLC/LDLC ratios might serve as a better indicator of lipid-related risk for cardiovascular disease in this population.

Participants eligible for the trial will undergo a structured interview administered by a trained fieldworker. The same questionnaire will be applied irrespective of the target condition reported by the participant, as data collected are applicable across all cohorts.

Data collected will include:

- Patient contact details to facilitate administration of follow-up interviews
- Demographic data (date of birth, sex)
- National identity numbers to permit linkage with the national mortality register, which is estimated to record more than 90% of all deaths in South Africa (Statistics South Africa 2005)
- Hospitalisation folder numbers, if available, to permit linkage with hospitalisation databases
- Measurement of cardiovascular risk parameters (e.g. blood pressure, waist circumference)

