- Processes of care received at the clinic: e.g. foot and eye examinations, counselling re weight loss and smoking cessation, referrals
- Medication received at the clinic (name, dose, duration)
- Dates prescriptions were filled at the clinic (to establish proportion covered by filled medication), as a proxy of adherence
- Health related quality of life (EuroQol 5D) to establish local utilities for a range of health states in those with chronic diseases for use in the economic model. The EuroQol has been widely used and validated in South Africa, and approved translations are available for the languages required for this study.
- Symptom severity: St Georges Respiratory Questionnaire (Jones 1991)
- Smoking history
- Health care utilisation (clinic visits, hospitalisations, use of private providers)
- Income and changes due to current illness
- WHO’s Disability Assessment Schedule II (Posl 2007)
- Expenditure on health care utilisation

The questionnaire is currently in development, and will be piloted prior to implementation in the trial. Once approved by the HREC it will be translated into Xhosa and Afrikaans in accordance with internationally accepted practices (Guillemin 1993). Certificates of translation will be submitted to the HREC.

Interviews will be conducted using computers, which we have previously used in similar field work data collection exercises in South Africa (Seebregts 2008). Based on previous experience with a similar questionnaire, interviews administered using such computers will last between 20 minutes and one hour, depending on the number of medications to be documented, and the extent of healthcare utilisation reported by the respondent.

Recruitment will occur during the month prior to the commencement of educational outreach and is estimated to last up to two weeks in each clinic. Patients will be re-interviewed once by appointment: approximately 12 months after the outreach training started (12 to 16 months after recruitment). Recruitment will start in March 2011and will be staggered across the 38 trial clinics .

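### The primary GEE model adjusts only for sub-district; a short pre-specified list of baseline covariates, mostly already collected, would be a low-cost improvement to a valid analysis

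*Combined protocol and SAP*

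**What the plan says.** The Data analysis section of the Integrated Care Guideline Trial states that "a logistic regression model will be used to evaluate the effect of the intervention with stratification as a co-factor", estimated by the "generalised estimating equations (GEE) approach which takes into account the clustering of patients within clinics". Study design identifies the stratum: "Clinics will be randomised within health sub-district strata". No section adds a baseline covariate to the primary model or plans a covariate-adjusted sensitivity analysis.

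The baseline interview for trial participants, described under Research procedures and data collection, includes "Measurement of cardiovascular risk parameters (e.g. blood pressure, waist circumference" and "Medication received at the clinic (name, dose, duration", together with the St George's Respiratory Questionnaire. CES-D 10 is scored for entry to the depression cohort.

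Baseline control does appear in the secondary analyses. Analysis (a) is an "analysis of the primary outcome but restricted to the subgroup of patients in whom control at baseline has been determined to be inadequate". Analysis (c) examines effect modification by control and adherence in hypertensive patients. Neither adjusts the primary estimate.

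On timing, "Randomisation will be carried out by the trial statistician before the intervention is implemented or patients recruited". Patient recruitment and data collection adds that patients are enrolled shortly before training starts in the intervention clinics of their sub-district.

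**The concern.** Treatment intensification is a change from the baseline regimen, so it has no baseline value of its own, but it has two obvious predictors. One is how poorly controlled the patient is. The other is what the patient already takes: someone already on aspirin cannot score the aspirin item in Table 1, and the same holds for the beta-agonist and ipratropium items. The ceiling is only partial. For hypertension, "Addition of new antihypertensive" stays open to treated patients, and dose increases count for several drug classes.

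Two things are at stake. Leaving out predictors that are already recorded may give up some precision. And with 19 clinics per arm, recruited into after randomisation, the arms can differ in case mix, and the stratum-only estimate carries that difference. The sections available do not say whether the fieldworkers who recruit are unaware of allocation, so the difference could exceed chance.

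**Working it through.** **1. The plan's own power, without covariates.** Inputs: rates, ICCs and cluster sizes from Table 1; 19 clinics per arm from Figure 3; 20% loss and two-sided testing from Endpoints and sample size calculations. Alpha is not stated; I take 0.05.

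With m analysed per clinic = 0.8 × cluster size, SE² = [p0(1−p0) + p1(1−p1)] × [1 + (m−1)ICC] / (19m), and power = Φ(|p1−p0|/SE − 1.96).

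| Cohort | p0, p1 | ICC | m | SE | Power |
| --- | --- | --- | --- | --- | --- |
| Diabetes; hypertension | 0.25, 0.36 | 0.04 | 48 | 0.0363 | 0.857 |
| Chronic respiratory | 0.15, 0.25 | 0.02 | 21.6 | 0.0329 | 0.859 |
| Depression | 0.04, 0.10 | 0.04 | 48 | 0.0201 | 0.846 |

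The stated 85% reproduces in every cohort with no covariate.

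**2. How strong could a covariate be?** The documents give no covariate-outcome correlation. The background section reports 33% of hypertensive patients controlled. With an overall intensification rate of 25%, and rates pu and pc in uncontrolled and controlled patients, ρ = (pu − pc) × √(0.67 × 0.33) / √(0.25 × 0.75).

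- If 15% of controlled patients are intensified, pu = 0.299 and ρ = 0.16.
- If none are, pu = 0.373 and ρ = 0.41. That end is extreme, because adding aspirin or a statin counts and need not depend on blood pressure.

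**3. Gain in power for hypertension and diabetes.** If a covariate explains ρ² of the within-clinic variance only, SE² = [p0(1−p0) + p1(1−p1)]/19 × [(1−ICC)(1−ρ²)/m + ICC]. Power moves from 0.857 to 0.860 at ρ = 0.16 and to 0.876 at ρ = 0.41.

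Simulated exchangeable logistic GEE with robust SE (38 clinics; strata omitted because their number is not given) allows for the covariate also varying between clinics, with an assumed covariate ICC of 0.04:

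- One binary severity covariate, 50 per clinic, 2,000 runs per setting. Severity odds ratios of 2, 3 and 5 correspond to ρ of about 0.13, 0.19 and 0.26. Power unadjusted and adjusted: 0.814 and 0.808; 0.806 and 0.808; 0.803 and 0.816.
- One continuous covariate, 48 per clinic, 1,500 runs per setting. Power: 89.2% and 90.1% at ρ = 0.24; 89.3% and 92.6% at 0.33; 88.4% and 94.0% at 0.43.
- A further run of the same kind gave gains of about 1, 2, 4 and 6 points at ρ = 0.14, 0.24, 0.33 and 0.41.

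The base levels differ between simulations because of the t reference distribution and the residual clustering assumed, so only the contrasts should be read.

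The SE of the adjusted log odds ratio rises (0.183 to 0.193 at severity odds ratio 5), but so does the conditional effect (0.522 to 0.565). The ratio goes from 0.522/0.183 = 2.85 to 0.565/0.193 = 2.93. Standardised back to the marginal scale, the SE falls by 0.5% to 3%.

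**4. Depression.** With one binary covariate, power was 0.756 unadjusted and 0.740 adjusted at odds ratio 2, and 0.755 and 0.734 at odds ratio 5: no gain.

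**5. Chance imbalance.** With 67% uncontrolled and an assumed ICC of 0.04 for baseline control, the SD of the difference between arms is √{2 × 0.67 × 0.33/19 × [0.96/48 + 0.04]} = 0.037, so 1.96 SD = 7.3 percentage points. The simulated slope of the unadjusted log odds ratio on this difference was 0.62 at severity odds ratio 2 and 1.32 at 5. The 95% extreme shift is therefore 0.62 × 0.073 = 0.05 to 1.32 × 0.073 = 0.10. The planned log odds ratio is ln[(0.36/0.64)/(0.25/0.75)] = 0.523, and the confidence interval half-width is about 1.96 × 0.182 = 0.36. Over repeated randomisations, the mean unadjusted estimate for severity odds ratios 2 to 5 was 0.522 to 0.524.

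**The case against.** The strongest reply is that nothing here is an error. A stratum-adjusted cluster GEE is a legitimate primary analysis, and its power claim stands without covariates. That is right. A reader might infer from the omission that the trial is underpowered or the analysis invalid; step 1 shows otherwise.

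A reader might also infer a gain of 8 to 9 points. That needs covariates explaining a quarter of the variance both within and between clinics, and no figure in the documents supports it. Nor does the gain extend to all four outcomes. In depression, the 4% control rate caps the correlation with a normally distributed score at about 0.44, CES-D 10 is already truncated at 10 by the entry rule, and the simulation showed no benefit.

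Calling the imbalance bias would also be too strong. What step 5 measures is sampling variation, which the cluster-robust interval already covers, and 0.05 to 0.10 is its 95% extreme.

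Two points survive. Recruitment after randomisation allows case-mix differences beyond chance, and unbiasedness over randomisations does not answer that; adjustment deals with the measured part, though not with unmeasured selection. And secondary analyses (a) and (c) answer different questions: (a) drops patients, and (c) tests effect modification.

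**Conclusion.** The omission is real, and its consequence is modest. The planned analysis is valid and meets its stated power. Adjustment would be worth roughly 0 to 2 points of power at correlations up to about 0.25 and 3 to 6 points at 0.33 to 0.43, with little or nothing for depression from CES-D 10 alone. The simulated gains are for the hypertension and diabetes inputs; the respiratory cohort was not simulated. The second benefit is an estimate corrected for measured case-mix differences in the realised sample, of order 0.05 to 0.10 in log odds ratio at the chance extreme.

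These sizes rest on assumed covariate strength, an assumed ICC of 0.04 for baseline control, alpha of 0.05, and the 33% control rate from an earlier survey in Cape Town health centres. Since the data are mostly collected anyway, this is an inexpensive improvement that the plan should make before outcomes are seen.

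**What to change.** In the trial's Data analysis section, add to the stratum a short pre-specified list of individual baseline covariates:

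- Hypertension: mean systolic blood pressure, number of antihypertensives, aspirin use, statin use.
- Diabetes: number of oral hypoglycaemics, and insulin, ACE inhibitor, aspirin and statin use. Leave out HbA1C unless its coverage is settled: Endpoints and sample size calculations limits it to 20 clinics, while Research procedures and data collection has it for all medicated diabetic participants.
- Chronic respiratory disease: St George's symptom score, beta-agonist use, inhaled corticosteroid use.
- Depression: baseline depression treatment; CES-D 10 optional.

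Report the odds ratio standardised to the population-average scale, with a named cluster-robust variance method suited to 38 clinics. Fix the functional form of each covariate and a simple rule for missing baseline values. Keep the stratum-only model as a sensitivity analysis. If the sponsor prefers to keep it as primary, the adjusted model should at least be named in advance as a supporting analysis, so that covariates are not chosen after imbalance is seen.

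The cost is a little more analysis work, with no new data, visits or patients. The one trap is that the adjusted odds ratio is conditional unless standardised, so the plan must say which is reported.

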### Characteristics of the study population

Clinics

Public-sector primary care clinics in the Eden and Overberg districts of the Western Cape province which provide care to underserved communities are characterised by high burdens of both infectious and chronic diseases. The 38 largest fixed facilities will be included in the trial (Appendix 1). These clinics service around or more than 10 000 attendances per year, and are staffed by nurse practitioners, doctors and community health workers, all of whom participate in care delivery for chronic diseases. The Eden and Overberg districts have been selected ahead of others, because doctors are in short supply, and services are provided mainly by nurses. This will allow the trial’s results to be generalisable to similar LMIC settings where non-physicians provide care.

Patients

Inclusion criteria:

- Age ≥ 18 years; and
- Planning to reside in the area for the next year; and
- Written consent to participate in the study

Four cohorts are defined. Patients may fulfil inclusion criteria for more than one cohort. Inclusion criteria based on target chronic disease:

| **Target condition** | **Inclusion criteria** |
| --- | --- |
| Hypertension | Self-reported hypertension requiring medication |
| Diabetes | Self-reported diabetes requiring medication |
| Chronic respiratory disease | Self-reported asthma/ chronic bronchitis/ emphysema requiring medication OR  Cough and/or difficult breathing >2 weeks (and not on treatment for tuberculosis in the past 3 months) |
| Depression | The Center for Epidemiologic Studies Depression Scale (CES-D 10 Scale) score of 10 or more (Andresen 1994) |

Exclusion criteria:

- Inability to meet the above criteria
- Acute and/or terminal condition precluding participation such as AIDS or cancer.
- Psychiatric diagnoses precluding participation such as schizophrenia, dementia and other cognitive impairment measured by self report or medical history.
- For chronic respiratory disease: patients who have received tuberculosis treatment in the preceding 3 months will be excluded.

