### Endpoints and sample size calculations

The primary endpoint selected for diabetes, hypertension and chronic respiratory disease is ***treatment intensification***, based on research that identifies clinician inertia as a key reason for failure to control these non-communicable chronic diseases (Van Bruggen 2009, Ho 2008, Rodondi 2006, Turchin 2008, Wang 2007). Definition of treatment intensification is dependent on the target condition (Table 1). For depression, ***case detection*** was selected as the primary outcome because the condition is grossly under diagnosed in primary care – as many as 1 in 5 people attending primary care services are suffering from a mental health condition, mostly depression, yet only 5% of those with the condition have been diagnosed.

Background rates and expected effect sizes for diabetes and hypertension were obtained from prior local and international research studies (Charlton 2008, Nau 2004, Grant 2007). Intracluster correlation co-efficients were drawn from published estimates from a number of cluster randomised controlled trials in each disease area (O’Connor, Fairall 2005, Morrell 2009, Rahman 2008). All sample size calculations are for two-sided tests and are powered at 85%. The sample sizes have been inflated by 20% to allow for losses to follow-up at the follow-up interview planned for 12-15 months after recruitment.

We anticipate substantial co-morbidity. Patients with more than one target condition will be eligible for more than one cohort. Based on reported levels on co-morbidity, we estimate that we will need to recruit 121 patients per clinic to realise the sample size for all cohorts (4598 patients in total).

Planned secondary endpoints include disaggregation of primary endpoints, measurement of other processes of care including screening for complications (e.g. dilated eye exams), monitoring control (e.g. annual HbA1C), symptoms (St Georges Respiratory Questionnaire), changes in risk factors for chronic diseases (e.g. systolic blood pressure, waist circumference), productivity, healthcare utilisation, cardiovascular events (e.g. stroke), mortality, newly commenced on simvastatin, and new diagnosis of hypertension , diabetes, chronic respiratory disease, TB and depression.

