Due to the considerable burden imposed by venesection, sample size estimates have also been completed for one of the secondary outcomes, HbA1C in diabetic participants. In order to show a difference of 0.5% (8.8% in the control group vs. 8.3% in the intervention group) we need to complete venesection on 30 diabetic patients in 10 clinics in each group (i.e. 600 diabetics from 20 clinics in total). This contains the logistical burden and cost associated with including HbA1C as a secondary outcome. In these calculations, we assumed a standard deviation in HbA1C of 1.2% from the ACCORD trial (Williamson 2007) and an intracluster correlation co-efficient of 0.05.

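### The primary GEE logistic analysis has 38 clinics and sub-district terms but no named small-sample method; with default robust inference the 5% tests would exceed 5% and the 95% intervals would be too narrow

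*Combined protocol and SAP*

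**What the plan says.** Under Study design, the allocation is described as "Clinics will be randomised within health sub-district strata". Under Characteristics of the study population, "The 38 largest fixed facilities will be included in the trial (Appendix 1"); the trial figure shows 19 clinics per arm.

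Under Data analysis in the trial section, "a logistic regression model will be used to evaluate the effect of the intervention with stratification as a co-factor". Then: "The model parameters will be estimated by the generalised estimating equations (GEE) approach which takes into account the clustering of patients within clinics", and "Odds ratios will be presented with 95% confidence intervals". That is the whole inferential specification for the four primary outcomes. No working correlation, variance estimator, finite-cluster correction or reference distribution is given. The later general Data analysis section only refers back to the individual study sections.

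On design, Endpoints and sample size calculations says "All sample size calculations are for two-sided tests and are powered at 85"%, and "The sample sizes have been inflated by 20% to allow for losses to follow-up". The same section plans HbA1C measurement on "600 diabetics from 20 clinics in total" as a secondary outcome, but gives only a sample size for it and no analysis model.

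**The concern.** GEE point estimates hold up reasonably well with few clusters. The usual robust (sandwich) variance does not: it is a large-sample approximation in the number of clusters, here clinics. Two things push in the same direction.

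- Fitted residuals are smaller than true errors, so the sandwich understates the variance. Treatment and stratum are both clinic-level covariates, so each stratum term uses up information from the 38 clinics.
- A normal reference ignores the uncertainty in a variance estimated from few clusters.

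An analyst who used this default would be following the plan as written, and would report p-values that are too small and intervals that are too narrow. One who chose a correction would also be following it. The choice changes interval width by up to about 30% in the scenarios below, so it should not be left until the data are in. All four primary comparisons use this model, and the Synopsis says that the provincial health department will use the results to guide further implementation.

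**Working it through.** **Inputs.** From the documents: 38 clinics, 19 per arm; two-sided tests at 85% power; 20% loss to follow-up. From Table 1 (control rate, intervention rate, ICC, cluster size): diabetes and hypertension 0.25, 0.36, 0.04, 60; chronic respiratory disease 0.15, 0.25, 0.02, 27; depression 0.04, 0.10, 0.04, 60. Completers per clinic: 0.8 × 60 = 48, and 0.8 × 27 = 21.6, about 22. Assumed: number of strata S.

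**1. The plan's own sample size.** Let n be the individually randomised size per arm (pooled two-proportion formula, two-sided 5%, 85% power). With 19 clinics per arm, 19m = n[1 + (m − 1)ICC], so m = n(1 − ICC)/(19 − n·ICC).

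- Diabetes, hypertension: n = 314; m = 301.44/6.44 = 46.8; /0.8 = 58.5 (stated 60).
- Respiratory: n = 286; m = 280.28/13.28 = 21.1; /0.8 = 26.4 (stated 27).
- Depression: n = 324; m = 311.04/6.04 = 51.5; /0.8 = 64.4, or × 1.2 = 61.8 (stated 60).

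At the stated sizes less 20%, the effective number per arm is 19 × 48/2.88 = 316.7 (respiratory: 19 × 21.6/1.412 = 290.7). Power is 85.4%, 85.4%, 85.6% and 84.3%. The design figures reproduce to within about a point. They presuppose a test that holds its 5% level.

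**2. A hand approximation for the default test.** With equal clinic sizes, the model has S + 1 clinic-level parameters, so average leverage is (S + 1)/38. The uncorrected standard error is then about k = √[(38 − S − 1)/38] of its true value. The actual error is about P(|t| > 1.96k) on 38 − S − 1 df. The properly calibrated interval is wider by a factor of about t₀.₉₇₅/(1.96k).

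| S | df | k | 1.96k | approx. error | t₀.₉₇₅ | width factor |
|---|---|---|---|---|---|---|
| 1 | 36 | 0.973 | 1.908 | 6.4% | 2.028 | 1.06 |
| 2 | 35 | 0.960 | 1.881 | 6.8% | 2.030 | 1.08 |
| 4 | 33 | 0.932 | 1.827 | 7.7% | 2.035 | 1.11 |
| 8 | 29 | 0.874 | 1.712 | 9.8% | 2.045 | 1.19 |
| 11 | 26 | 0.827 | 1.621 | 11.7% | 2.056 | 1.27 |

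**3. Simulation.** Beta-binomial clinics, stratified allocation, arm plus stratum terms, between-stratum SD 0.3 on the logit scale, 2,500 trials per cell (simulation error about 0.4-0.7 points). Ranges are across the three distinct outcome settings.

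| S | clinic-size CV | default sandwich, normal: error | Kauermann-Carroll, t: error | width factor | Kauermann-Carroll, t: power |
|---|---|---|---|---|---|
| 2 | 0 | 6.6-7.8% | 4.7-5.8% | 1.08 | 81.9-82.4% |
| 2 | 0.5 | 6.0-10.2% | 4.2-7.2% | 1.09-1.10 | 76.0-79.4% |
| 4 | 0 | 7.5-9.2% | 4.8-6.2% | 1.12 | 82.0-83.8% |
| 4 | 0.5 | 8.8-11.4% | 5.3-7.2% | 1.13-1.14 | 76.1-80.8% |
| 8 | 0 | 9.8-11.0% | 4.7-5.8% | 1.20-1.21 | 80.4-81.7% |
| 8 | 0.5 | 10.6-12.4% | 4.5-6.6% | 1.22-1.24 | 76.0-79.7% |
| 11 | 0 | 12.2-13.6% | 5.2-6.1% | 1.27-1.28 | 80.2-81.3% |
| 11 | 0.5 | 12.6-15.0% | 5.3-5.7% | 1.29-1.31 | 74.6-78.6% |

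A companion set of runs gave 6.1-8.4% with one stratum and 15-16% with 15. A further independent run with equal clinic sizes and 3,000 trials per cell gave 6.4-7.7% (S = 1), 6.9-8.1% (2), 7.2-7.9% (4), 9.5-10.9% (8) and 11.5-13.4% (11). A spot check with packaged exchangeable GEE and robust errors (S = 8, CV 0.5, only 150 trials) gave 8.7%, with a standard error of √(0.087 × 0.913/150) = 2.3 points. That is consistent.

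Mancl-DeRouen with a normal reference fell to about 2-3% at 11 strata, so the choice of correction matters too.

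**The case against.** The strongest reply is that the section is brief rather than wrong: it names no variance estimator, so nothing commits the trial to an uncorrected sandwich. That stands. A reader might infer that the plan relies on one, but the documents neither state it nor rule it out. The supported point is that the choice is open and that a common default would be anti-conservative.

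Other stronger readings also fail.

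- **False positives at two to three times the nominal rate.** That means 10-15%, and it needs roughly 8 or more strata. With 1 to 4 strata the excess is mostly 1 to 4 points. The stratum count may follow from the facility list in Appendix 1, which is not in the reviewed text.
- **The 20-clinic HbA1C comparison is worse still.** The GEE logistic model is assigned to the primary outcome. HbA1C is continuous and has no stated model, so there is no specified method to fault.
- **Provincial roll-out hangs on these p-values.** Background section 3.3 describes a provincial commitment to integrated guidelines for 2011, and the benefits section places the trial alongside incremental implementation. The results inform further implementation but are not its sole basis.

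It is also fair to say that Kauermann-Carroll is one acceptable option among several, and that it still reached 6-7% in some depression scenarios.

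What survives is that every stratum count tried gave error above 5%, including a single stratum, and nothing elsewhere in the documents fills the gap.

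**Conclusion.** The concern holds as a conditional one. If the primary GEE models are analysed with the usual uncorrected sandwich and a normal reference, the nominal 5% tests run at about 6-8% with one stratum, 6-10% with 2, 7-11% with 4, 9-12% with 8 and 11-15% with 11. The 95% intervals are correspondingly too narrow.

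The direction is secure, because the hand approximation and the simulations agree. The size depends mainly on the number of sub-district strata, and then on how unequal the clinics are and how rare the outcome is; depression is the most exposed.

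The figures assume one model term per stratum, beta-binomial clinics at the Table 1 ICCs, and size CVs of 0 or 0.5. Strata with no events were dropped in the tabulated runs. Runs that failed for separation were excluded in the companion set, mainly for the 4% outcome with many strata.

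**What to change.** Amend the trial's Data analysis section so that all p-values and confidence intervals from the primary-outcome GEE models use a named small-sample method. One suitable choice is a Kauermann-Carroll bias-corrected sandwich with a t reference on (clinics − strata − 1) degrees of freedom, where clinics and strata are those contributing to that cohort. Name the working correlation, state the number of strata, and say what happens to a stratum with no events. Add a permutation test that re-randomises clinics within strata as a check. State the HbA1C analysis model; the same correction is needed there only if that model is GEE.

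This takes a few sentences and no new data. The real cost is precision. Intervals are about 8-10% wider with 2 strata, 11-14% with 4, 20-24% with 8 and 27-31% with 11. Power is about 80-84% with equal clinic sizes and 75-81% with a size CV of 0.5, against the stated 85%. Part of the lower figure comes from unequal clinic sizes, not from the correction. The stated power should be recalculated on the chosen method and restated. The higher apparent power of the uncorrected test is no argument for it, because that test does not hold its level.
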